**Fig. 1 Fig1:**
[figure not shown]
Pathways contributing to the development of micro- and macro-vascular complications in patients with T2DM and insulin resistance (only coronary artery disease, retinopathy and nephropathy are illustrated). Red boxes Indicate where the trial’s primary objective (potential molecular effects of empagliflozin on inflammatory state) will be assessed. The concept was derived from the studies of Bugger et al. and Oguntibeju et al. [15, 16]. *IL-6* interleukin 6, *IL-1* interleukin 1, *ROS* reactive oxygen species, *CRP* C-reactive protein, *GBM* glomerular basement membrane, *LDL* low density lipoprotein, *WBC* white blood cell, *PDGF* platelet derived growth factor, *TGF-β* transforming growth factor beta

**Table 1 Tab1:** Trial objectives and measurement methods (measured at time = 0 and after 26 weeks of treatment)

Objective	Definition
Primary	1. To investigate the impact of empagliflozin on plasma IL-6 level in patients with T2DM patients and coronary artery disease (established by coronary angiography)
Secondary	1. Inflammatory biomarkers Changes in serum hs-CRP levels Changes in plasma IL-1b levels 2. Oxidative stress status Changes in lymphocytic reactive oxygen species Changes in plasma levels of malondialdehyde Changes in plasma carbonyl levels Changes in plasma antioxidant capacity Changes in plasma reduced glutathione levels Changes in catalase enzyme activity Changes in plasma superoxide dismutase enzyme activity 3. Platelet function Changes in CD62-P expression on the platelet surface 4. Glycemic status Changes in fasting blood glucose levels Changes in HbA_1c_ levels Changes in HOMA-IR

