#### Randomization and follow-up

The randomization method employed in this study is stratified randomization. During the screening process, eligible patients are stratified by gender (male and female), age (45–54, 55–64, and 65–75 years old), and HbA_1c_ (6.5–7.9% and 8–9.5%) and assigned into one of the two arms of the study (A or B). The randomization sequence is created using Winpepi software (version 11.6). The allocation sequence was concealed using the sealed envelopes mechanism. All participants will be followed up by phone calls every 4 weeks for assuring the proper medication usage, and for premature discontinuation or development of any adverse events. At the end of weeks 2, 12, and 26, patients are instructed to attend clinic visits for complete checkup and physical examination. Patients are also advised to return all used and unused medications at the end of week 26. The study’s follow-up and procedures are summarized in Table 3.

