#### Primary outcome

The primary outcome of this study is the changes in plasma interleukin 6 levels after 26 weeks of the treatment between the two study arms.

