#### Statistical analysis plan

We will use the means ± standard deviations (SD) and frequencies and percentages n (%) to interpret the results. The noninferiority margin and 95% confidence interval (CI) will be estimated for primary outcomes. The noninferiority will be accepted if the upper 95% CI for the relative risk (RR) lies below the margin of noninferiority. An intention-to-treat analysis will be used to examine the effect of missing data. Superiority analysis will be performed at α = 0.05 level. The interaction effects will be examined using graphical and statistical tests. The Kolmogorov–Smirnov test will be used to determine the normality of the distribution of continuous quantitative data. Independent T-test will be used (on condition of normal distribution) for statistical analysis of quantitatively continuous variables findings related to primary and secondary outcome including interleukin 6 levels, oxidative stress biomarkers, platelet function, glycemic status, cardiac biomarkers, echocardiographic finding, hematopoietic and renal biomarker, lipid profile and electrocardiographic parameters. The Mann–Whitney U test will be used on the condition of abnormal distribution. Chi-square test will be used to analyze qualitative data such as ST segment deviation and T-wave changes in electrocardiogram. We will consider the probability of 0.05 for the main analysis. We will perform Bayesian analysis of the covariance test to examine the effects of intervention on IL-6. The primary outcome is considered as confirmatory and the secondary outcomes are considered as exploratory. All statistical tests will be carried out in the in Rv.4 environment. The primary data of the FFQ will be evaluated by using the Nutritionist software version 4 (N4).

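### The test named for IL-6 adjusts for neither baseline IL-6 nor the randomisation strata, and its rank against the planned Bayesian analysis of covariance is not fixed

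*Protocol article*

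**What the plan says.** The Primary outcome section defines the endpoint as "changes in plasma interleukin 6 levels after 26 weeks of the treatment between the two study arms". Table 1 gives the timing for all outcomes: "measured at time = 0 and after 26 weeks of treatment". So a baseline value exists for IL-6 and for every other continuous outcome.

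Under Randomization and follow-up, "eligible patients are stratified by gender (male and female), age" (three bands) and HbA1c (two bands). That makes 2 × 3 × 2 = 12 strata.

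The Statistical analysis plan names the tests: "Independent T-test will be used (on condition of normal distribution) for statistical analysis of quantitatively continuous variables findings related to primary and secondary outcome". Its list of variables includes IL-6. The alternative is also unadjusted: "The Mann–Whitney U test will be used on the condition of abnormal distribution". Nothing in the section brings the stratification factors into an analysis.

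The same section adds: "We will perform Bayesian analysis of the covariance test to examine the effects of intervention on IL-6". It calls the primary outcome confirmatory and the secondary outcomes exploratory, but does not say whether the confirmatory conclusion on IL-6 comes from the t-test or Mann–Whitney, or from the Bayesian model.

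**The concern.** A two-sample test on change subtracts baseline with a fixed coefficient of one. Unless ρ is close to one, that over-corrects: measurement noise and regression to the mean in the baseline value stay in the error term. Regression on baseline estimates the coefficient instead. It also corrects the estimate for whatever chance difference in baseline IL-6 the arms show. The stratification factors raise a similar issue. If they predict IL-6, leaving them out makes the standard error larger than the design warrants.

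At stake are the width of the confidence interval and the power for the single confirmatory outcome, in a trial expecting about 40 evaluable patients per arm. Two IL-6 analyses without a stated order also leave open which one decides the result if they disagree.

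**Working it through.** **Inputs from the article.** Difference 4.45 pg/mL and SD 8.9 pg/mL (Sample size calculations); 50 per arm with 20% dropout, hence 50 × 0.8 = 40 evaluable per arm; alpha 0.05 (Statistical analysis plan).

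**Assumptions.** Two-sided testing; equal variances at week 0 and week 26; ρ between 0.3 and 0.8, since the article gives no value. The article does not say whether 8.9 is the SD of a level or of a change, so both readings are shown. All figures are normal-theory, on the raw scale.

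**The plan's own figure.** The standardised difference is 4.45/8.9 = 0.5. An unadjusted two-sample comparison with 80% power at alpha 0.05 needs 63 (normal approximation) or 64 (t) per arm two-sided, and 50 or 51 one-sided. The stated 41 does not reproduce. At 41 per arm and SD 8.9, two-sided power is 61%. The sample size is a separate matter; it is relevant here because it leaves little precision to spare if 8.9 is the SD that applies to the test.

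**Formulas.** With σ the SD of the level:
- variance of the change: 2σ²(1−ρ)
- residual variance after regression on baseline: σ²(1−ρ²)
- ratio, ANCOVA to change score: (1−ρ²)/[2(1−ρ)] = (1+ρ)/2, which is 0.65, 0.75, 0.85 and 0.90 at ρ = 0.3, 0.5, 0.7 and 0.8

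Power is from the noncentral t distribution with noncentrality 4.45/(s√(2/40)) and 78 degrees of freedom, where s is the relevant SD. For s = 8.9 the noncentrality is 0.5/0.2236 = 2.236, and power is 60%.

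**Reading A: 8.9 is the SD of the level**

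| ρ | SD, change | SD, ANCOVA | Power, change | Power, ANCOVA |
|---|---|---|---|---|
| 0.3 | 10.53 | 8.49 | 46% | 64% |
| 0.5 | 8.90 | 7.71 | 60% | 72% |
| 0.7 | 6.89 | 6.36 | 81% | 87% |
| 0.8 | 5.63 | 5.34 | 94% | 96% |

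**Reading B: 8.9 is the SD of the change.** The ANCOVA SD is then 8.9√((1+ρ)/2).

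| ρ | SD, ANCOVA | Power, change | Power, ANCOVA |
|---|---|---|---|
| 0.3 | 7.18 | 60% | 78% |
| 0.5 | 7.71 | 60% | 72% |
| 0.7 | 8.21 | 60% | 67% |
| 0.8 | 8.44 | 60% | 64% |

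**Cost in degrees of freedom.** Baseline 1, sex 1, age bands 2, HbA1c band 1: 5 in total. Using 73 instead of 78 degrees of freedom lowers power by about 0.1 percentage point in every row.

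**Strata.** If the three factors explain 5% to 20% of the residual variance (an assumption), an interval that omits them is wider by 1/√(1−0.05) = 1.026 to 1/√(1−0.20) = 1.118, or about 3% to 12%.

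**The case against.** Several objections are sound and limit the point.

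- A reader might infer that the test ignores baseline. It does not: the outcome is a change, so baseline enters by subtraction. The comparison is change score against regression adjustment, and under reading A the gap falls to 2 points at ρ = 0.8.
- A reader might infer that the Bayesian analysis of covariance has no part in the decision. The article gives it no rank in either direction. Its missing covariate list is detail that a condensed article may leave to a fuller plan, and is not criticised here.
- A reader might conclude that the trial is underpowered. That is conditional. Under reading A the change-score test reaches 81% at ρ = 0.7.
- The unadjusted estimate is unbiased under randomisation, and an unadjusted test after stratified randomisation is valid and, if anything, conservative. Chance imbalance matters only conditionally on the baseline observed.
- An SD of 8.9 beside a mean of 6.6 suggests skew. The plan's rule might then select Mann–Whitney, and a log-scale model would not carry a 4.45 pg/mL difference. The power figures describe neither case.
- The secondary outcomes are declared exploratory, so the same model there is a preference.

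What these objections leave standing is that the article positively names an unadjusted test for its confirmatory outcome, so this is not simply an omission left to another document. ANCOVA is also the more precise analysis under both readings of 8.9 and at every ρ shown.

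**Conclusion.** The point holds as one of efficiency and of specification, not of validity. The named tests leave unused a baseline already collected and the factors on which randomisation was stratified, and the order of the two IL-6 analyses is open.

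Adjusting for baseline alone gains 18, 12, 6 and 2 percentage points of power at ρ = 0.3, 0.5, 0.7 and 0.8 if 8.9 is the SD of the level, and 18, 12, 7 and 4 points if it is the SD of the change. The direction is secure given equal variances at the two times. The size rests on an assumed ρ, the unstated meaning of 8.9, two-sided testing and normal theory on the raw scale. Any further gain from the strata depends on how far they predict IL-6, which the article does not give. The documents do not support calling the planned test biased, or the trial underpowered without those conditions.

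**What to change.** Name one confirmatory analysis of IL-6: ANCOVA of the week-26 value (log scale if skewed) on treatment, baseline IL-6, sex, age and HbA1c. Use main effects rather than 12 stratum terms. Continuous age and HbA1c are acceptable. Continuous age also avoids a band that is undefined for ages 40–44: Table 2 admits patients from 40, while the recruitment text and the strata start at 45, and those passages need reconciling.

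State that the Bayesian analysis of covariance is supportive, or make it the primary analysis with these covariates. Keep the t-test and Mann–Whitney as sensitivity analyses. Preferably use the same model, each with its own baseline, for the exploratory continuous secondary outcomes.

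The cost is analysis wording and about 5 degrees of freedom. The covariates are already collected. The change should be fixed before the treatment codes are broken.

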### Statistical considerations

#### Sample size calculations

The sample size was estimated based on the changes in plasma IL-6 level as a primary outcome of treatment. According to a previous study, the SGLT2-i dapagliflozin reduced the mean plasma IL-6 level from 6.6 to 5.8 (pg/mL) with the standard deviation (SD) of 8.9 [17]. The minimal important difference (MID) of the IL-6 level was calculated 4.45 (pg/mL) using 0.5 × SD (the distributional-based method) [18]. With a study power of 80%, an alpha level of 0.05%, and MID of 4.45, the required sample size was calculated to be 41 patients in each arm. Considering a 20% dropout during the study, the sample size was rounded up to 50 participants in each arm. The sample size was calculated using the G-power software (version 3.1.9.2).

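### The only confirmatory outcome, IL-6, has two analyses of the treatment effect and the plan does not say which is the main one, so control at 0.05 is not assured

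*Protocol article*

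**What the plan says.** All of this stands in one paragraph of the protocol article, under Statistical analysis plan.

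- **Status of the outcome:** "The primary outcome is considered as confirmatory and the secondary outcomes are considered as exploratory". The primary outcome is the change in plasma IL-6 over 26 weeks, compared between arms (Primary outcome section).
- **Error level:** "Superiority analysis will be performed at α = 0.05 level", and later "We will consider the probability of 0.05 for the main analysis". Neither sentence gives sidedness or names the analysis.
- **First analysis of IL-6:** "Independent T-test will be used (on condition of normal distribution", with IL-6 listed by name among many continuous outcomes. Otherwise, "The Mann–Whitney U test will be used on the condition of abnormal distribution". A Kolmogorov–Smirnov test decides between them.
- **Second analysis of IL-6:** "We will perform Bayesian analysis of the covariance test to examine the effects of intervention on IL-6".

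No analysis of IL-6 is labelled primary, supportive or sensitivity, and no other section settles which one decides.

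**The concern.** The 0.05 level protects a confirmatory claim only if the deciding analysis is fixed beforehand. Here the treatment effect on IL-6 is to be estimated in two ways that target different quantities: an unadjusted comparison of means or ranks, and a covariate-adjusted difference. The two can disagree. IL-6 makes that more likely, because the planning figures (mean 6.6 pg/mL, "with the standard deviation (SD) of 8.9") put the SD above the mean of a marker that cannot be negative, which points to strong right skew.

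If the two results split, the text lets either be defended as the main analysis. The trial's only confirmatory claim would then rest on a choice made after the results are known.

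**Working it through.** **1. Inputs from the protocol article.** Level 0.05 (Statistical analysis plan); IL-6 mean 6.6 and SD 8.9 pg/mL, 41 per arm before dropout and 50 after (Sample size calculations). The per-arm numbers serve only as simulation sizes. Whether 41 follows from its stated inputs is a separate matter, as is the alpha printed there as a percentage, read here as 0.05.

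**2. Assumptions, because the article does not give them.**
- Each analysis is two-sided.
- The Bayesian ANCOVA has a flat prior and is positive when its 95% interval excludes zero. It then coincides with the ordinary ANCOVA at p < 0.05.
- The t-test or Mann–Whitney test is applied to the change from baseline.
- The baseline to week-26 correlation is 0 to 0.9 for normal data and 0.3 to 0.7 for lognormal data.

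**3. Skew implied by the planning figures.** For a lognormal variable, σ² = ln(1 + (SD/mean)²) = ln(1 + (8.9/6.6)²) = ln(2.818) = 1.036, so σ ≈ 1.02 on the log scale. The lognormal runs at 50 per arm used a log-scale SD of 1.

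**4. The plan's own figure, with one analysis deciding.** Under no effect and with normal data, the t-test alone rejected in 4.6–5.2% of runs and the ANCOVA alone in 4.8–5.3%. The stated 0.05 is reproduced.

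**5. Either analysis may carry the claim, no true effect.**

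| Data | Per arm | Correlation | False-positive rate |
|---|---|---|---|
| Normal, t-test or ANCOVA | 41 | 0 / 0.3 / 0.5 / 0.7 / 0.9 | 8.2 / 8.2 / 7.5 / 6.5 / 6.0% |
| Normal, t-test or ANCOVA | 50 | 0 / 0.3 / 0.5 / 0.7 / 0.9 | 8.2 / 7.6 / 7.5 / 6.9 / 5.7% |
| Lognormal, Mann–Whitney or ANCOVA | 50 | 0.3 / 0.5 / 0.7 | 7.9 / 7.7 / 7.7% |
| Lognormal, Kolmogorov–Smirnov-selected test or ANCOVA | 40 | 0.3 / 0.5 / 0.7 | 7.5 / 7.1 / 7.1% |

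There were 20,000 runs per normal scenario, 8,000 per lognormal scenario at 50 per arm and 4,000 at 40 per arm. For comparison, two independent tests would give 1 − 0.95² = 9.75%. The rates here are lower because both analyses use the same data.

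**6. What a single better-suited analysis would do.** For lognormal IL-6, 41 per arm and correlation 0.3 to 0.7, ANCOVA of log week-26 IL-6 adjusted for log baseline holds about 5% error. For a 25% reduction (an assumed effect, not the trial's planning effect), power is about 26–43%, against about 14–27% for the Kolmogorov–Smirnov-selected test on the change. These runs adjusted for baseline only, not for the stratification factors.

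**The case against.** The strongest reply is that the frequentist test is the natural main analysis. The 0.05 sentence comes directly after the frequentist tests and the Bayesian sentence follows it. The sample size is built on power and alpha. A 0.05 threshold does not apply to a posterior distribution. Read that way, the Bayesian ANCOVA is supportive and 0.05 is kept. This stands in part: the order of the sentences leans towards the frequentist test. It does not settle the matter, because the Bayesian sentence is the only test sentence devoted to the intervention effect on IL-6, and it comes directly before the statement that the primary outcome is confirmatory.

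Two stronger readings are tempting and are not supported:

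- **That the 0.05 error rate is not held.** A reader might infer this from the presence of two analyses. The article states no rule that success follows if either is positive, so the inflation is conditional on such use.
- **That three tests are available to choose from.** The t-test and the Mann–Whitney test are alternatives under a stated condition, so a rate counting both alongside the ANCOVA does not describe this plan.

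It is also fair to say that the prior and the posterior threshold belong in a full analysis plan. Their absence from an article is not a defect, and this point does not rest on it. An informative prior could move the error rate up or down.

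Blinding does not answer the point. The Blinding section has analysts working with groups A and B, so whether A differs from B under each method is visible without unblinding.

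**Conclusion.** The point holds in limited form: the deciding analysis of the only confirmatory outcome is not named, so control at 0.05 is not assured. With one analysis designated, the false-positive rate is about 5%. If either could carry the claim, it is about 7–8% for lognormal IL-6 and about 6–8% for normal data, on the flat prior, 95% interval rule and correlations assumed above. The exact inflation cannot be derived from the document. The excess is moderate, but it falls on the trial's single confirmatory claim.

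**What to change.** Before unblinding, name one confirmatory analysis of IL-6 at two-sided 0.05. Preferably this is ANCOVA of log week-26 IL-6 on treatment, log baseline IL-6 and the factors used to stratify randomization (sex, age group, HbA1c group). Label the Bayesian ANCOVA and the t-test or Mann–Whitney test as supportive, with no bearing on the success claim.

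Naming any one of the listed analyses would be enough to secure the error rate. The log-scale ANCOVA is preferred because it needs no normality pre-test to choose the method, suits a marker whose SD exceeds its mean, and uses a baseline that is already measured.

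The cost is one or two sentences and no new data. The Current status section describes recruitment as still open, with 91 patients randomized by 9 November 2020, so at that stage the wording could be settled ahead of results. The small downside is that the effect is reported as a ratio of geometric means instead of a difference in pg/mL.

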### Current status

At present, the mentioned sites are actively recruiting patients. The pre-recruitment phase (evaluation and extraction of 8000 patients’ medical records from hospitals and clinics registries) was started on November 11, 2019. The patients’ recruitment phase (the first patient who was consented and randomized) was started on June 29, 2020 and until November 9, 2020, 91 patients were randomized. The end date of expected recruitment may be extended due to the COVID-19 pandemic but it is expected that the recruitment phase will ends by the end of January 2021.

## Discussion

The EMPA-CARD randomized placebo-controlled clinical trial seeks to investigate the mechanisms underlying the cardiovascular effects of empagliflozin in patients with T2DM who have proven CAD at the same time.

Most of the recent published clinical trials have focused on the effects of empagliflozin in patients with heart failure in which the superiority of empagliflozin has been reported. The recent meta-analysis with the pooled population of 8474 patients (DAPA-HF and EMPEROR-Reduced population) showed that treatment with an SGLT2-i was associated with a significant reduction in cardiovascular death (pooled hazard ratio of 0.86) and re-hospitalization due to heart failure complications as well as improvements in renal function [19]. However, limited data are available regarding the beneficial effects of empagliflozin in patients with established CAD. The EMPA-HEART Cardiolink-6 trial showed that 6 months of treatment with empagliflozin significantly reduced left ventricular mass index (LVMi) in patients with T2DM and CAD [20]. In this study we are exploring molecular mechanisms and cellular changes that potentially mediate these beneficial effects. Plasma levels of IL-6, a pro-inflammatory cytokine which also has anti-inflammatory properties promotes and regulates inflammatory processes in patients with T2DM, and changes in its level is considered as the primary outcome of this study. The rationale of choosing this biomarker as a leading factor for investigation among other candidates is that IL-6 and tumor necrosis factor-alpha (TNF-α) appear to have the highest impact on the promotion of CAD in patients with diabetes mellitus [21]. Moreover, the other factors measured in this study are either directly or indirectly affected by IL-6. It has been shown that IL-6 reduces oxidative stress and apoptosis of pancreatic β-cell by promoting autophagy, an adaptive response to cellular stress. Previous human studies have shown that concomitant treatment with empagliflozin and metformin in patients with type 1 diabetes reduced IL-6 up to 1.34 fold and improved anti-oxidative status parameters comprising of total anti-oxidative status (TAS) for up to 1.07 fold and superoxide dismutase (SOD) for up to 1.08 fold. It has also been suggested that the cardio-protective effects of this drug class may be associated with its anti-oxidative effects, including normalizing interferon-γ (IFN-γ), TNF-α and IL-6 levels especially with empagliflozin [22, 23]. In animal studies, diabetic rats which were treated by SGLT2 inhibitor had a lower development of endothelial dysfunction, oxidative stress, advanced glycation end products/ receptor for advanced glycation end products (AGE/RAGE) signaling and inflammation due to inhibition of the activity of NADPH oxidase and decreased serum levels of the AGE precursor methylglyoxal [24]. In a study by Tahara et al. diabetic rats which were treated by ipragliflozin had significantly lower plasma levels of IL-6, TNF-α, monocyte chemoattractant protein-1 (MCP-1), and CRP [25]. Nevertheless, it seems that the inflammation and fatty acid oxidation, which are also promoted by IL-6, have greater impact on increasing the oxidative stress in patients with T2DM. This could enhance the rate and magnitude of coronary atherosclerosis and subsequent CAD [26, 27].
